**FIGURE 2 eph13615-fig-0002:**
[figure not shown]
Data collection timeline. HRV, heart rate variability. JISC is a digital platform designed specifically for education and research organizations that can be used for the creation and dissemination of surveys. BL, baseline; PRE‐1, immediately after pre‐task somatosensory gating measure; PRE‐2, immediately after pre‐task somatosensory attenuation measure; POST‐1, immediately after the completion of the task (cognitive or physical); POST‐2, immediately after post‐task somatosensory gating measure; POST‐3, immediately after post‐task somatosensory attenuation measure.

On completion of the participant characteristics and validated measures, participants will be given a unique, randomly generated four‐digit identifier. Consent forms, which will contain the participants personal details, will be saved separately from all other data and only identified with the participants four‐digit identifier.

The protocol is split into two testing sessions. Each session is expected to take up to 90 min. The two sessions are identical, except that in one session participants perform a cognitive task and in the other session they perform a physical task. Participants will be asked to complete both sessions in a crossover design. In each session, somatosensory processing (attenuation and gating) will be measured pre‐ and post‐task (physical or cognitive). The order of the two sessions will be randomized using the command randi([1 2]) in MATLAB software version 23.2 (MathWorks Inc., Natick, MA, USA), which will be run on the morning of the first testing session. A value of ‘1’ indicates that cognitive task will be performed first and ‘2’ indicates that the physical task will be performed first. Participants will be asked to return on a separate day for each session.

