In the original study (Hassan et al., 2024), each cognitive task was performed for 10 min at a time and was repeated three times, resulting in a total duration of 2 h (four tasks × 10 min per task × three repeats = 4 × 10 min × 3 = 120 min). In the present study we will reduce the duration of each task to 2 min, giving a total duration of 24 min (four tasks × 2 min per task × three repeats = 4 × 2 min × 3 = 24 min). This has been done in consultation with our patient and public involvement group to avoid placing excessive burden on a population that reports high fatigue levels. The modified duration is expected to induce fatigue as participants are required to task switch between multiple short‐duration tasks, constituting an additional demand that increases cognitive fatigue (Dang et al., 2013). Testing of this modified task in 15 young healthy individuals indicates a significant increase in fatigue from pre‐ to post‐task. Fatigue measured on a 100 mm visual analogue scale (VAS) increased from a mean (standard error) of 26 (5) mm pre‐task to 59 (5) mm post‐task (Student's paired *t*‐test *t* = −7.251; *P* < 0.001). Fatigue measured using the fatigue subscale of the Brunel Mood Scale increased from a median (interquartile range) of 7.0 (1.5) pre‐task to 9.0 (4.0) post‐task (Wilcoxon signed rank test *Z* = 2.991; *P* = 0.003) ([name] and [name], unpublished data; Figures 3 and 4). Participants will be sent a training version of this protocol prior to attending the lab session, and this will allow them to familiarize themselves with the tasks involved to minimize any learning effect during the testing session. The cognitive task will be completed on a computer that will be placed in front of participants. Full details of the task are in Supporting information, Appendix 2.

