Hypothesis 2: State fatigue following exertion will be predicted by somatosensory attenuation at baseline, somatosensory gating at baseline, the presence of long COVID (long covid/controls), and the type of task (cognitive/physical). Performance fatigability will be considered a moderator variable in these relations. State fatigue prior to exertion will be included as a covariate in this analysis.

This will be tested using a linear mixed model:

$$Y_{ijk}=\mu +a_{i}+b_{j}+c_{k}+d_{ik}+e_{ik}+f_{ik}+g_{ijk}+\left(f_{ik}\times a_{i}\right)+\left(f_{ik}\times b_{j}\right)+\varepsilon_{ijk}$$
where:

*Y_ijk_
*: state fatigue following exertion in the *i*‐th group (long COVID/control) during task *j* (cognitive/physical) for the *k*‐th subject.μ: the overall mean of state fatigue following exertion.
*a_i_
*: the effect of the *i*‐th group (fixed effect: long COVID vs. control).
*b_j_
*: the effect of the *j*‐th task (fixed effect: cognitive vs. physical).
*d_ik_
*: the baseline somatosensory attenuation for the *k*‐th subject in the *i*‐th group.
*e_ik_
*: the baseline somatosensory gating for the *k*‐th subject in the *i‐*th group.
*f_ijk_
*: the performance fatigability for the *k*‐th subject in the *i*‐th group during the *j*‐th task.
*g_ijk_
*: the state fatigue prior to exertion for the *k*‐th subject in the *i*‐th group during the *j*‐th task (covariate).(*f_ik_
*×*a_i_
*): the interaction term between performance fatigability and group.(*f_ik_
*×*b_j_
*): the interaction term between performance fatigability and task.
*ϵ_ijk_
*: the residual error term, assumed to be normally distributed.
Hypothesis 3: The change in somatosensory attenuation (Research Question 3a) and somatosensory gating (Research Question 3b) from pre‐ to post‐task will be predicted by the change in state fatigue from pre to post, fatigability, the presence of long COVID (long COVID/controls), and the type of task (cognitive/physical).

We will use linear mixed models to test these hypotheses, with separate models for somatosensory attenuation and somatosensory gating:

$$Y_{ijk}=a_{i}+b_{j}+c_{ijk}+d_{ijk}+u_{0i}+\varepsilon_{ijk}$$
where:

*Y_ijk_
*: attenuation or gating at baseline in the *i*‐th group (long COVID/control) during task j (cognitive/physical) for the k‐th subject.
*a_i_
*: the fixed effect of the *i*‐th group (long COVID vs. control) on baseline attenuation.
*b_j_
*: the fixed effect of the *j*‐th task (cognitive vs. physical) on baseline attenuation.
*c_ijk_

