#### Planned exploratory analysis

3.7.1

Hypotheses 1, 2, 3 will be rerun with age included as a covariate.Hypotheses 1, 2, 3, 4 will be rerun with time of day (morning/afternoon) at which participants completed sessions and session order (cognitive/physical first) included as additional predictor variables.The effect of autonomic dysfunction during exertion, on state fatigue pre‐ to post‐exertion, via an effect on somatosensory processing post‐exertion will be tested using mediation analysis with separate models for somatosensory attenuation and somatosensory gating. This will be quantified in participants with and without long COVID.The relations between autonomic dysfunction during exertion, state fatigue during exertion, and perceived effort during exertion will be quantified in participants with and without long COVID during both tasks (cognitive/physical). This will be tested using correlation analysis.Test‐retest reliability will be conducted for each somatosensory processing measure (gating and attenuation), from the baseline measure from each session (cognitive/physical). This will provide a measure of whether somatosensory processing is stable over time.

We will carry out outcome neutral criteria that must be met for successful testing of the stated hypothesis. This includes checking for the absence of floor or ceiling effects. This will be done by examining data distributions to ensure that there are no extreme values that could impact the validity of results. Additionally, we will investigate the quality of the data and this will include frequency measures and the shape of the distribution.

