### Sample size

3.8

The study is powered to address Research Question 1a. Previous research indicates an effect size of 0.78 for differences in somatosensory attenuation between young and older individuals (Parthasharathy et al., 2022). Powering the current study to detect an effect size of 0.78 between two independent means for Research Question 1a—somatosensory attenuation in individuals with and without long COVID—with an α error probability of 0.05 and a power of 95% and based on a non‐directional two‐tailed hypothesis requires 44 participants per group (G*power 3.1.9.7). Dropout is not expected to impact Research Question 1a or 1b, as it involves initial measurements during the first session. However, there is a potential for dropout to impact the subsequent research questions, which rely on participants returning for a second session.

The sample size gives us power of 90% to detect an effect of 0.70 between two groups at two repeated time points with alpha error probability of 0.05 for Research Questions 2 and 3, or a power of 80% to detect an effect of 0.60. A dropout rate of 10% would mean that our power to detect these effect sizes decreases to 60%. The approach for addressing Research Questions 2 and 3 ensures that the study is adequately powered to detect correlations of 0.50 and 0.40, respectively. The code used to calculate the outcome measure is available at https://github.com/smancuso/R‐ Code/blob/cc90c623c4dc733fe5c93ef5a795dde010152c63/Power.R

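### The Hypothesis 2 and 3 crossover models have no first/second-session (period) term, and the planned session-order rerun cannot adjust the task effect for one

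*Protocol article*

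**What the plan says.** All references are to the protocol article.

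- **Design (3.3 Experimental procedures).** "Participants will be asked to complete both sessions in a crossover design", on separate days. Allocation to order: "The order of the two sessions will be randomized using the command randi([1 2]) in MATLAB". This is one unblocked draw per participant, so the two orders need not come out equal.
- **Hypothesis 2 (3.7 Statistical analysis).** "This will be tested using a linear mixed model". Its terms are group, task ("fixed effect: cognitive vs. physical"), a term indexed by subject that the legend does not define, baseline attenuation, baseline gating, fatigability, state fatigue before exertion, and the fatigability-by-group and fatigability-by-task interactions.
- **Hypothesis 3 (3.7).** The terms are group, task, change in state fatigue, fatigability and a random intercept.
- **Rerun (3.7.1 Planned exploratory analysis).** Hypotheses 1 to 4 are refitted with time of day and "session order (cognitive/physical first) included as additional predictor variables".

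Neither main model has a first/second-session term. No period variable and no order-by-task interaction is named anywhere.

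**The concern.** Task is a named predictor in Research Questions 2 and 3. If responses differ between a participant's first and second session, whichever task comes second carries that difference. In a crossover a period term separates this from the task effect. The plan has no such term, and the variable it does add describes the person's sequence, not the session.

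The protocol itself treats learning as possible: a training version of the cognitive battery is sent out to "minimize any learning effect during the testing session" (3.3.1), treadmill familiarisation is allowed (3.3.2), and test-retest stability of the somatosensory measures is to be examined (3.7.1). At stake are the precision of the task coefficient in Hypotheses 2 and 3 and, when the orders are uneven, its value.

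**Working it through.** **1. The plan's own sample size.** Section 3.8: "Powering the current study to detect an effect size of 0.78 between two independent means", two-sided alpha 0.05, power 95%, 44 per group. The exact noncentral-t calculation gives 94.7% power at 43 per group and 95.1% at 44, so 44 is reproduced. The point below does not depend on it; it uses only N = 88.

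**2. Why session order cannot adjust the task contrast.** Let τ be the task effect (physical minus cognitive) and π the period effect (second minus first session). A participant's difference, physical minus cognitive, has mean τ + π if cognitive came first and τ − π if physical came first. Without a period term the task estimate is the average difference, with expectation

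τ + π × (n cognitive-first − n physical-first) / N.

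Session order takes the same value in both of a person's records, so it drops out of the difference. In one simulated data set (true task effect 5 mm, period effect 10 mm, 53:35 split, no time-varying covariates) the task estimate was:

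| Model | Task estimate (mm) |
|---|---|
| No order term | 7.400 |
| Session order added | 7.400 |
| Period added | 5.382 |
| Order by task, effect-coded | 5.382 |

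The first two agreed whether or not the model had a subject intercept. With fatigability and its interactions in the model, adding session order moved the task estimate by at most 0.07 mm in any simulated trial.

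**3. How uneven the orders may be.** Under Binomial(88, 0.5):

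- exact 44:44 balance: 8.5%
- mean absolute imbalance: 8.5% of N
- 95% range: 35 to 53 cognitive-first
- 50:38 or worse: 24%
- 54:34 or worse: 4.2%

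**4. Size.** The protocol gives no period effect, so 0.5 and 1 within-person SD (σ) are assumptions. The setting is a plain two-period crossover with complete data, no covariates and no true task effect.

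*Precision at 44:44.* The difference has noise variance 2σ². An omitted period effect π adds π². The standard error is therefore too wide by √((2 + (π/σ)²)/2):

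- π = 0.5σ: √(2.25/2) = 1.061, about 6%.
- π = 1σ: √(3/2) = 1.225, about 23%. In units of σ this is √(3/88) = 0.185 against √(2/88) = 0.151.

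*Conditional bias at 54:34.* The imbalance is (54 − 34)/88 = 0.227.

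- π = 0.5σ: bias 0.227 × 0.5 = 0.11σ; simulated false-positive rate about 9.5%.
- π = 1σ: bias 0.23σ; simulated rate about 18%.

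*At 48:40, close to the mean imbalance.* The imbalance is 8/88 = 0.091, so the bias is about 0.05σ and 0.09σ. The false-positive rates are about 4.7% and 3.6%, so there is no inflation.

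*Over the planned random allocation.* Mean bias is about zero and the Type I error was 4.7% to 4.9% for period effects of 0.25σ to 1σ. A period term brought the rate to about 5% in every setting checked, including conditionally on the 54:34 split.

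**The case against.** The strongest reply has four parts.

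- **Randomised order protects the level of the test.** This stands. A reader might infer that the planned task test has an inflated false-positive rate, but over the allocation in the protocol it does not. The 9.5% and 18% rates are conditional on a split that, with anything worse, has a 4.2% chance. It would be wrong to attach to them the 17% chance of a 27:17 or worse split within a single group of 44, because task is one pooled term over all 88 participants.
- **The planned models remove part of a session shift.** This stands in part. The Hypothesis 2 covariate for state fatigue before exertion may absorb some of a general shift. The Hypothesis 3 outcome, read as the pre-to-post change stated in the hypothesis, cancels a constant shift between sessions. Neither removes a period effect on the response to the task, such as a smaller fatigue rise on the second visit. The training version and familiarisation may reduce such an effect but do not exclude it.
- **The reach is narrow.** This stands. Research Question 1 uses only the first session. With complete data each person contributes both periods, so group and other between-person contrasts are essentially unaffected.
- **Session order has a use.** This stands. It can show a sequence or carry-over difference, and for Hypotheses 1 and 4, with one record per person, it is the workable coding. A reader might infer that the whole rerun is mistaken; the protocol does not support that. The gap is only that session order does not adjust the task contrast in Hypotheses 2 and 3.

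**Conclusion.** The point holds in a limited form. The written models omit period, and the only planned order adjustment cannot supply it. The sure cost, if a period effect exists, is precision: a task standard error about 6% too wide at 0.5 within-person SD and 23% at 1 SD. The further cost is conditional bias equal to the period effect times the proportional order imbalance, on average about 8.5% of the period effect and about 20% at the edge of the 95% range (53:35, 18/88 = 0.20). Unequal loss of second sessions could add to the imbalance.

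These figures rest on assumed period effects and a plain crossover without the planned covariates; the relevant period effect is the one on the response to the task. This is a worthwhile correction to the secondary models, not a flaw in the powered comparison.

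**What to change.** - In 3.7, add period (first/second session) as a fixed effect beside task in the Hypothesis 2 model and in both Hypothesis 3 models.
- In 3.7.1, keep session order for Hypotheses 2 and 3 as a separate sequence or carry-over check, and say that it does not adjust the task effect for period.
- For Hypotheses 1 and 4 leave session order as written: period would be constant in Hypothesis 1 and undefined in Hypothesis 4.

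The cost is one degree of freedom per model and a line of wording. No new data are needed, since each participant's order is fixed by the recorded draw.

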## RESEARCH QUESTIONS

2

Research Question 1: Are pre‐task (baseline) somatosensory attenuation (Research Question 1a) and somatosensory gating (Research Question 1b) different between individuals with long COVID fatigue compared to controls?

Research Question 2: Is state fatigue following exertion predicted by somatosensory attenuation at baseline, somatosensory gating at baseline, the presence of long COVID (long COVID/controls), and the type of task (cognitive/physical), and is performance fatigability a moderator variable in this relation? State fatigue prior to exertion will be included as a covariate in this analysis.

Research Question 3: Is the change in somatosensory attenuation (Research Question 3a) and somatosensory gating (Research Question 3b) from pre‐ to post‐task predicted by the change in state fatigue during exertion, fatigability, the presence of long COVID (long COVID/controls), and the type of task (cognitive/physical)?

Research Question 4: Among individuals with long COVID, is trait fatigue predicted by the increase in state fatigue induced by a physical task, the increase in state fatigue induced by a cognitive task, mood, illness beliefs, autonomic symptoms and autonomic nervous system function?

This study will provide the first comprehensive investigation into the role of somatosensory processing in long COVID fatigue and explore how prominent symptoms in long COVID (autonomic dysfunction, altered mood, beliefs about the meaning of symptoms) interact with somatosensory processing, fatigability and the experience of fatigue.

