#### State fatigue

3.4.2

State fatigue will be evaluated using a 100 mm VAS that asks participants to rate their current level of fatigue. The VAS will be anchored on the left side with ‘not fatigued at all’ and on the right side with ‘extremely fatigued’ (Supporting information, Appendix 3).

Participants will be asked to make a line on a paper copy of the VAS at six time points across each testing session: at baseline (BL), immediately after the pre‐task somatosensory gating measure (PRE‐1), immediately after the pre‐task somatosensory attenuation measure (PRE‐2), immediately after the completion of the task (cognitive or physical) (POST‐1), immediately after the post‐task somatosensory gating measure (POST‐2), and immediately after the post‐task somatosensory attenuation measure (POST‐3) (Table 1 and Figure 2). This is to allow evaluation of the time course of fatigue and recovery of fatigue over the period required for the outcome measures. State fatigue at each time point will be quantified as the distance of the mark made by the participant from the left‐edge of the horizontal line (range 0−100 mm).

**TABLE 1 eph13615-tbl-0001:** Outcome measures.

		Time point of measurement		
Concept	Measure	Prior to first testing session	Cognitive task testing session	Physical task testing session
Severity of trait fatigue	FAS CFQ‐11 total CFQ‐11 physical subscale CFQ‐11 mental subscale	Prior to session		
Impact of trait fatigue	MFIS physical subscale MFIS cognitive subscale MFIS psychosocial subscale	Prior to session		
Autonomic symptoms	COMPASS‐31	Prior to session		
Mood	HADS‐A HADS‐D	Prior to session		
Illness beliefs	BIPQ	Prior to session		
Autonomic function	HRV		During somatosensory attenuation measure and throughout cognitive and physical task	During somatosensory attenuation measure and throughout cognitive and physical task
State fatigue	Visual analogue scale		BL, PRE‐1, PRE‐2, POST‐1, POST‐2, POST‐3	BL, PRE‐1, PRE‐2, POST‐1, POST‐2, POST‐3
State fatigue	Numeric rating scale		After every fourth task and at the end of the cognitive task	90 s, 180 s and 270 s and at the end of the 6MWT
Perceived effort	Rating of perceived exertion scale		After every fourth task and at the end of the cognitive task	90 s, 180 s and 270 s and at the end of the 6MWT
Cognitive fatigability	BIS		During cognitive task	
Physical fatigability	Average walking speed from 330 to 360 s of 6MWT minus average walking speed from 30 s to 60 s			During physical task

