Somatosensory attenuation	Mean force overcompensation at each target force Intercept and slope from a linear regression of matched versus target force		Pre‐ and post‐task	Pre‐ and post‐task
Somatosensory gating	*I* _50_rest_ − *I* _50_movement_		Pre‐ and post‐task	Pre‐ and post‐task

Abbreviations: BIPQ, Brief Illness Perception Questionnaire; BIS, Balanced Integration Score; BL, Baseline; CFQ‐11, Chalder Fatigue Questionnaire; COMPASS‐31, Composite Autonomic Symptom Score; FAS, Fatigue Assessment Scale; HADS‐A, Hospital Anxiety and Depression Scale anxiety subscale; HADS‐D, Hospital Anxiety and Depression Scale depression subscale; HRV, heart rate variability; MFIS, Modified Fatigue Impact Scale; POST‐1, immediately after the completion of the task (cognitive or physical); POST‐2, immediately after the post‐task somatosensory attenuation measure; POST‐3, immediately after the post‐task somatosensory gating measure; PRE‐1, immediately after pre‐task somatosensory attenuation measure; PRE‐2, immediately after pre‐task somatosensory gating measure.

In addition, state fatigue will be reported using a numerical rating scale (NRS) at four time point during the physical and cognitive tasks. This will be at 90, 180 and 270 s of the 6MWT and after every fourth task in the cognitive task and at the end of each task. In the cognitive task these ratings will be time stamped. Participants will be shown the NRS, which consists of a scale from 0 to 10, with 0 being anchored as ‘not fatigued at all’ and 10 being anchored as ‘extremely fatigued’. They will be asked to verbally report the number that corresponds to their fatigue level. The need to switch from a VAS to an NRS is dictated by the inability of participants to physically mark a line on a piece of paper while completing the 6MWT.

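### The exploratory mediation analysis names no post-task fatigue reading, and none of those collected lets a pre- to post-exertion change be read as mediated by post-exertion somatosensory processing

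*Protocol article*

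**What the plan says.** Section 3.7.1 of the protocol article lists this exploratory analysis: the influence of autonomic dysfunction during exertion on pre- to post-exertion state fatigue "via an effect on somatosensory processing post‐exertion will be tested using mediation analysis", with one model for attenuation and one for gating, in participants with and without long COVID. The exposure is autonomic dysfunction during the task, the mediator is processing after the task, and the outcome is the fatigue change across the task. No visual analogue scale (VAS) reading is named for the post value.

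Three readings could serve. Section 3.4.2 and the Figure 2 legend place POST-1 directly at the end of the task. The Figure 2 legend then gives "POST‐2, immediately after post‐task somatosensory gating measure; POST‐3, immediately after post‐task somatosensory attenuation measure". The Table 1 footnote gives the other order: "POST‐2, immediately after the post‐task somatosensory attenuation measure; POST‐3, immediately after the post‐task somatosensory gating measure". Section 3.4.2 explains the repeated readings: "This is to allow evaluation of the time course of fatigue and recovery of fatigue over the period required for the outcome measures".

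The opposite direction is also planned. Research Question 3 asks whether the change in processing is "predicted by the change in state fatigue during exertion", and Hypothesis 3 models it. The Figure 1 legend proposes that state fatigue and processing act on each other in both directions.

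**The concern.** A mediator has to act after the exposure and before the outcome. If the fatigue change closes when the task ends, and processing is measured only afterwards, the variable called the mediator is recorded after the outcome it is meant to explain. An association between the two would then fit fatigue altering processing at least as well as processing altering fatigue, and the protocol itself puts forward that reverse path.

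The stake is interpretive. The Figure 1 legend postulates that autonomic dysfunction reaches fatigue through somatosensory processing, and the Introduction says that no study has looked at this chain. The Hypothesis 4 model has no somatosensory term, so this mediation is the only planned analysis of that pathway. A significant indirect effect would probably be read as support for it. The study is a registered report, so the permitted interpretation is best fixed before results are seen.

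**Working it through.** **1. Order of events.** Section 3.4.7 expects gating to take 20 min and attenuation 10 min. Approximate times after the end of the task are:

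| Event | Figure 2 legend and section 3.4.2 | Table 1 footnote |
|---|---|---|
| POST-1 | 0 min | 0 min |
| First measure | gating, 0 to 20 min | attenuation, 0 to 10 min |
| POST-2 | 20 min | 10 min |
| Second measure | attenuation, 20 to 30 min | gating, 10 to 30 min |
| POST-3 | 30 min | 30 min |

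POST-1 precedes both mediators in either column. PRE-2 is the last reading before the task in either column.

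**2. Which reading is meant.** Section 3.7.1 does not say. Research Question 3 describes its fatigue predictor as change during exertion, and Hypothesis 3 describes the same predictor as change from pre to post. The article thus treats the two as one quantity, and POST-1 is the reading that closes exertion. This is an inference from usage, not a stated definition.

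**3. Each candidate reading in turn.**
- POST-1: recorded before both mediators.
- POST-2: recorded after the first measure but before the second, so it cannot serve both models.
- POST-3: recorded after both. But POST-3 minus PRE-2 = (POST-1 minus PRE-2) + (POST-3 minus POST-1). The first bracket is the task-induced rise, which came before the mediator. Only the second follows it.

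**4. Can the model separate the directions?** With exposure X, processing M and fatigue change Y, the chain X to M to Y with a direct X to Y path has three paths for three correlations. So does X to Y to M with a direct X to M path. Both reproduce the correlations exactly, so fit cannot choose between them.

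**5. Size, as an illustration.** The article states no figure for this analysis and no correlations, so those below are assumptions. Let the truth be the reverse path only: X to Y with correlation r, Y to M with correlation s, and no effect of M on Y. The mediation model then estimates
- a = r × s for X to M;
- b = s(1 − r²) / (1 − r²s²) for M to Y given X.

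With r = s = 0.5: a = 0.25, b = 0.375 / 0.9375 = 0.40, and a × b = 0.10, although the true mediated effect is zero. With r = s = 0.3: a = 0.09, b = 0.273 / 0.9919 = 0.275, and a × b = 0.025.

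Mediation was declared when a and b were both significant at 0.05 (3,000 simulated data sets per cell, normal variables). The sizes are 44 (one group) and 88 (both groups). The 44 comes from section 3.8 and reproduces: a two-sample t-test with effect size 0.78, two-sided alpha 0.05 and power 95% needs 44 per group (power 0.951).

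| r | s | n = 44 | n = 88 |
|---|---|---|---|
| 0.3 | 0 | 0.2% | 0.2% |
| 0.3 | 0.3 | 3.3% | 9.5% |
| 0.3 | 0.5 | 15.3% | 27.9% |
| 0.5 | 0 | 0.4% | 0.2% |
| 0.5 | 0.3 | 5.7% | 20.1% |
| 0.5 | 0.5 | 32.1% | 64.4% |

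Without a fatigue-to-processing link, false declarations are rare. With one, they become more frequent as the sample grows.

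**The case against.** Four arguments weigh against this point.

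- **The reading is not fixed.** A reader might infer that the protocol makes the fatigue change complete before the mediator is measured. It does not say so: two of the three post-task readings follow a somatosensory measure, and section 3.3 groups fatigue with the other post-task measures. This stands, and the stronger statement should not be made. It does not rescue the analysis, because no single reading yields a pre- to post-exertion change that lies wholly after the mediator. A condensed article may leave the choice of reading to a fuller plan, but that choice would not cure the path as described.
- **Time of measurement is not time of occurrence.** Processing may shift during the task, and the post-task measure may be an imperfect proxy for that shift. This is fair, and it means that mediation is not ruled out. But the data cannot tell such a proxy from a consequence of fatigue.
- **Fitting both directions is declared.** A reader might see Hypothesis 3 as contradicting the mediation. It does not: the Introduction and the Figure 1 legend propose a two-way relation. The consequence is only that this analysis cannot say which direction it has found.
- **The analysis is exploratory, and the rates rest on assumed correlations.** Both stand. The rates show that the error can occur, not how often it will occur here.

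**Conclusion.** The point holds in a limited form. The mediation leaves its post reading unnamed. Under the natural reading (POST-1), the outcome is recorded before either mediator, and this does not depend on which documented order is right. Under a later reading, the change still includes the rise that preceded the mediator. Since the protocol also posits fatigue acting on processing, an indirect effect would not identify mediation. Under the assumed correlations of 0.3 to 0.5, a purely reverse path passes as mediation in about 3% to 32% of analyses with 44 participants and 10% to 64% with 88.

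Exact delays for each mediator cannot be given while the two orders conflict; only the overall span of about 30 min is common to both. It would be wrong to infer that the main results are at risk: the study is powered for Research Question 1a, and no numbered research question depends on this analysis.

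**What to change.** Report the pre- to post-exertion analysis as association only, with no claim of mediation or direction. This costs a change of wording in section 3.7.1.

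If a time-ordered analysis is wanted:
1. Reconcile the order of gating and attenuation between the Figure 2 legend with section 3.4.2 and the Table 1 footnote, because it decides which reading follows which mediator.
2. For each model, take as outcome the VAS reading made directly after that mediator, adjusted for PRE-2 and POST-1.
3. State that this model concerns fatigue in the 10 to 30 min after the task, that is, recovery, and not the task-induced rise.

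All these readings are already collected, so no new data are needed. The real cost is that the time-ordered model answers a different question from the one now posed. Pre-task processing is no substitute mediator: it is measured before an exposure that is defined during exertion, so it cannot carry that exposure's effect.
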